### Participant timeline

The outcome measures will be measured before and after the intervention phase and 8 weeks follow up. Specifically for the amblyopic cohort, the outcome measures will be performed at 5 time points (Fig. 2): pre-training A (T1), post-training A (T2), 8-weeks follow up training A and pre-training B (T3), post-training B (T4), 8-weeks follow up training B (T5). For the control cohort, the outcomes will be measured at 3 time points (Fig. 3): pre-training (T1), post-training (T2), 8-weeks follow up (T3). Certified and experienced orthoptists (4 and 35 years of experience) will perform the assessments of the primary outcome measure (BCVA) and the basic-vision secondary outcome measures (see below). The orthoptists will be masked to the randomization, i.e., the order of the treatment (AB or BA). The remaining secondary outcomes (functional vision, selective attention, motor control) will be assessed by the research team. Before the start of the treatment, the research team will set up the VR games at the participant’s home. Participants will receive a manual with instructions on how to use the VR games, and access to a website with instructional videos.

**Fig. 2 Fig2:**
[figure not shown]
Flowchart of the study procedures and assessments for the amblyopic cohort. Left path would be the order AB and right path BA. Green represents the VR intervention and orange represents standard care intervention. Outcome measures are assessed immediately before and after each intervention and at 8-weeks follow-up

**Fig. 3 Fig3:**
[figure not shown]
Flowchart of the study procedures and assessments for the control cohort. This cohort only completes the VR intervention. Outcome measures are assessed immediately before and after the intervention and at 8-weeks follow-up

### Sample size

We calculated the sample size necessary to obtain a significant difference (α = 0.05) between our treatment and refractive correction based on medium effect size (F’s Cohen = 0.25) with 80% power for a crossover design immediately after the intervention on our primary endpoint. This estimation resulted in a total sample of 24 individuals with residual amblyopia. To account for the potential dropout, we will increase the sample size by 25%, resulting in 30 individuals with amblyopia. We will additionally recruit 30 age-matched typically developing individuals to undergo the serious game VR-training. This sample will serve to account for the potential changes in vision, selective attention and motor control which are known to occur in healthy adults after a VR-training.

### Recruitment

The amblyopic cohort will be identified through referrals by ophthalmologists and optometrists from the Neuro-ophthalmology, Strabismus and Pediatric Ophthalmology Unit of the Dept. of Ophthalmology, HUG, and other private clinics. The control cohort will be recruited via printed flyers at public venues, schools, and colleagues’ children and friends. Recruitment will occur across the Geneva, Vaud, and Valais cantons. Participants will be offered to participate in the study once we are sure they meet all inclusion criteria without fulfilling any exclusion criteria. Before entering the study, written informed consent from all parents or caregivers and patients older than 14 years old will be obtained. Additionally, verbal assent will be obtained from participants between 6–14 years old. Through the insurance taken by the HES-SO Valais (sponsor of the study), the participants are insured for possible injuries as a result of their participation in the study.

## Methods II: Assignment of interventions

### Allocation

The amblyopic cohort will be randomly allocated to a treatment order (AB, BA) according to type of amblyopia (anisometropic, strabismic, mixed) and informed about the order by the research team. The allocation sequence will be generated with computer-generated random numbers, that will be created by an independent person of the project and uploaded to REDCap (concealed allocation with “sealed envelopes”). Only the research team will have access to the randomization instrument in REDCap. Whilst our sample size calculation is 30 participants in the amblyopic cohort (the control cohort will not be randomized), we have created a list with 10 additional cases. With this, in case we have unplanned dropouts, we will be able to continue with the original allocation list.

### Masking

The participants are not masked to the treatment order. Primary and secondary endpoint assessors of clinical data (orthoptists conducting the evaluation of the visual function), as well as the statistical analyst, will be masked to treatment order assignment. The research team, evaluating attention and motor function, are not masked as they also conduct the intervention. Nevertheless, these measures are objective and computerized, thus minimizing bias due to lack of masking.

## Methods III: Data collection, management, and analysis

### Data collection

All assessors will be trained to collect the study data. We have developed a handbook specific for the AMBER RCT in which all information related to the protocol is described and every study member has access to it.

The data will be collected at HUG (Geneva, Switzerland) and at the patients’ home (data collected directly from the Vivid Vision Home software and diary). General patient’s characteristics, such as age, sex and dominant eye will be recorded at baseline. Participants in the amblyopic cohort will be classified according to their type of amblyopia (anisometropic, strabismic or mixed).

All efforts will be made to promote participant retention and complete the crossover design of the study. We will phone the participants weekly while they are receiving the VR-based intervention and collect data related to their compliance and adverse events. All participants will fill in a diary in which they will report, if they have played the games of the intervention, as well as other games (and how many hours), to keep track of potential confounders. These data will be used to inform about participant retention in the study outcomes.

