This study protocol describes the setup for a Randomized Controlled Trial (RCT) comparing the effects of a personalized, VR, and home-based binocular stimulation intervention in people with residual amblyopia compared to standard care and to healthy controls. The first objective is to examine whether VR game-based interventions are not inferior to refractive correction in residual amblyopia and whether it will result in similar or better retention of the improvements. Secondly, we aim to explore whether such VR-derived improvements in the amblyopic cohort are beyond the changes we find in the control cohort. Lastly, we will study the underlying neural mechanisms of improvements by measuring brain activity and will ascertain whether such mechanisms can predict, in combination with clinical measures, treatment outcome.

This RCT will address the following research aims:a) test the efficacy of a serious game-based binocular stimulation in a VR environment in improving Best Corrected Visual Acuity (BCVA), compared to refractive correction in individuals with residual amblyopiab) test the potential VR-based benefits on clinical measures of other vision skills like stereoacuity, functional vision (i.e., reading skills), and suppression, compared to refractive correction in individuals with residual amblyopiac) test the potential benefits of VR-based training on visual and audiovisual selective attention and motor control skills, compared to refractive correction and to the control groupd) evaluate the adherence and safety of the VR-based intervention compared to standard caree) test the potential VR-based benefits on eye-related quality of lifef) test the potential VR-based benefits on cortical responses including visual, higher cognitive processes of audio-visual, and motor control skills in both cohortsg) test whether the potential VR-derived benefits on vision, attention and motor control skills in residual amblyopic patients are larger from those found in the control cohorth) identify clinical and electrophysiological factors predicting treatment response in individuals with residual amblyopia.

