At the beginning of the training, the visual contrast of objects visible to the fellow eye is decreased relative to the amblyopic eye. Each week and according to the participant’s performance, the difference in the input strength between the eyes will become smaller. The goal is to no longer need any modification of images’ features to combine them, and to perceive depth all the time. The difficulty of the games will be automatically adjusted based on an algorithm developed by Vivid Vision Inc. and integrated in the software (Smart Assist). This automatic adjustment aims at individualizing the treatment to meet the therapeutic needs of the patient. By individualizing the treatment to the patient’s needs, we hope to improve the efficacy of the treatment. To this purpose, built-in tests in the Vivid Vision Home software (Prism Tuner—to optimize the virtual prism settings for a patient’s treatment session, Stereoacuity – to estimate of the patient’s stereoscopic vision) will be performed systematically to increase or decrease the amount contrast needed for the patient to successfully play. These changes aim to keep the games challenging to the current level of visual skills of the participants. This “adaptiveness” of the games’ difficulty levels is meant to keep participants engaged and to support their improvement over the course of the whole training. Additionally, after each training session, participants or participants’ parents will report in a gaming diary, which they have been given by the experimenters, duration of their gaming session that day, their feelings about it (i.e., experiencing fun or, alternatively, difficulty during the game) as well as any adverse event (i.e., nausea, headache, diplopia). Participants will be instructed to inform the research team as soon as they experience any adverse event. Through the web-based dashboard of Vivid Vision Home, the research team will be able to see the participant’s activities, follow up on the prescribed play time and will get a notification after 2 days have passed without playing.

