## Secondary outcomes IV: Adherence and safety

Adherence (total amount of training hours, regularity of training) throughout the treatment will be investigated and the visual outcome will be correlated to the adherence that is automatically recorded by the Vivid Vision Home system. By including these measures of adherence to the serious games intervention, we will obtain important information [62], as the traditional treatment is known to have low adherence [11].

At the end of the study, the frequency and type of adverse events will be analyzed and compared across groups by the researcher masked to group allocation.

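### Aim d compares safety and adherence of VR with standard care, but active adverse-event solicitation and adherence recording are described only for VR, so the safety contrast is probably biased against VR

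*Protocol article*

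**What the plan says.** Among the research aims in the Background, aim d is to "evaluate the adherence and safety of the VR-based intervention", with standard care named as the comparator. The Adherence and safety section (Secondary outcomes IV) adds that "the frequency and type of adverse events will be analyzed and compared across groups by the researcher masked to group allocation".

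The collection rules are these:

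- **Calls.** Data collection: "We will phone the participants weekly while they are receiving the VR-based intervention and collect data related to their compliance and adverse events".
- **Diary with an adverse-event item.** Under the experimental intervention for the amblyopic cohort, participants or parents "will report in a gaming diary, which they have been given by the experimenters" the length of play and how it felt, "as well as any adverse event (i.e., nausea, headache, diplopia". It is filled in after training sessions.
- **Diary for everyone.** Data collection also states: "All participants will fill in a diary in which they will report, if they have played the games of the intervention, as well as other". The sentence ends with gaming outside the trial and its hours, and its stated purpose is to track confounders.
- **Adherence.** The measures named are hours trained and how regular the training was, recorded automatically by the VR software.
- **Glasses period.** The control-intervention section says glasses are worn for the same 8 weeks. It mentions no call, adverse-event prompt or record of wear.

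**The concern.** A difference in adverse-event frequency between two treatments can be interpreted only if events are sought in the same way under both. Here the contact schedule follows the treatment. Headache, which the diary names, can also occur without VR, and frequent questioning in one period will tend to pick up more of it there.

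Two features of the design might seem to protect the comparison, but neither does. Masking the researcher who compares events acts after the data exist, whereas this imbalance arises at collection. The crossover does not cancel it, because the extra questioning goes with VR in both sequences.

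At stake is a stated secondary aim, not the primary outcome. VR could appear less well tolerated than it is. The adherence half of the aim could end with a VR figure and nothing described to set beside it. Symptoms not asked about during the glasses period cannot be recovered at analysis.

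**Working it through.** The plan states no figure on this point, so there is none to reproduce. The check is a count of solicitation occasions followed by an illustration under stated assumptions.

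**1. Solicitation per 8-week period (from the documents)**

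| | VR | Glasses |
|---|---|---|
| Diary entries with an adverse-event item | 5 days x 8 weeks = 40, at one per prescribed day | none described |
| Weekly calls | 8 | none described |
| Total | 40 + 8 = 48 | none described |
| Adherence measure | software log | none described |

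These are occasions for asking, not detection rates.

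**2. Effect on the observed contrast**

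Let p be the true risk of an event in either period, and let d_VR and d_G be the proportions of events captured. The observed risks are p x d_VR and p x d_G, so:

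- apparent risk ratio = d_VR / d_G
- spurious risk difference = p x (d_VR - d_G)

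Assumptions, none of them in the documents: d_VR = 0.90; d_G = 0.60 or 0.30; p = 0.2 or 0.4.

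- d_G = 0.60: risk ratio 0.90/0.60 = 1.5. Risk difference 0.2 x 0.30 = 0.06, or 0.4 x 0.30 = 0.12.
- d_G = 0.30: risk ratio 0.90/0.30 = 3.0. Risk difference 0.2 x 0.60 = 0.12, or 0.4 x 0.60 = 0.24.

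For example, a true 20% risk in both periods would be observed as 18% on VR and 6% to 12% on glasses.

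**3. Chance of a falsely significant difference**

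This used a within-patient simulation with 20,000 runs per setting, independent periods, equal true risk and an exact McNemar test at 0.05. The test is my choice, as the article names none for adverse events. Sample sizes are the article's 24 (calculated) and 30 (recruited).

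| True risk | Capture on glasses | n = 24 | n = 30 |
|---|---|---|---|
| 0.2 | 0.90 (equal) | 0.016 | 0.021 |
| 0.2 | 0.60 | 0.029 | 0.041 |
| 0.2 | 0.30 | 0.089 | 0.148 |
| 0.4 | 0.90 (equal) | 0.026 | 0.026 |
| 0.4 | 0.60 | 0.082 | 0.109 |
| 0.4 | 0.30 | 0.351 | 0.462 |

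With equal capture the expected risk ratio is 1.0 and the false-positive rate stays below 0.03. With unequal capture the expected excess falls on VR.

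**The case against.** Several points on the other side are fair.

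- **Glasses-period events are not shown to be uncollected.** A reader might infer that they are. But all participants keep a diary that could run outside VR play, visits T2 and T4 close both treatment periods, and the Monitoring section has adverse-event forms checked with no restriction to VR. This stands, and the point is therefore under-solicitation. It does not remove the imbalance: the all-participant diary is described by games and hours only, Monitoring deals with events once known, and the calls are expressly confined to VR.
- **The comparison across groups may mean amblyopic versus healthy participants.** Both cohorts play VR, so solicitation could be the same. The wording allows this, and the Adherence and safety section does not itself compare adherence with standard care. The standard-care comparison rests on aim d, which is explicit.
- **An article condenses.** Data collection refers to a study handbook, so glasses wear may be recorded. It would be wrong to say that it is not measured; the article only fails to describe it. The limit on the calls, by contrast, is a stated rule and not an omission.
- **The bias would not hide harm from VR.** True: it runs against VR. At a 20% true risk, the chance of a falsely significant result is also modest.
- **Calls are part of a supported home programme.** Adding them to the glasses period makes that period differ slightly from usual care. This is a real but small cost.

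A reader might also infer that weekly contact on VR alone biases visual acuity through motivation. The documents give no basis for sizing that effect, and this point does not rely on it.

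**Conclusion.** The point holds in a limited form. Aim d promises a comparison of safety and adherence with standard care, while the described adverse-event solicitation and adherence recording apply to VR only. Glasses-period events would probably be under-ascertained, and the expected direction of the resulting bias is against VR. No comparator measure for adherence is described.

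The size cannot be derived from the documents. The risk ratio of 1.5 to 3.0 depends entirely on the assumed capture of 90% against 30-60%. The false-positive chances also depend on the assumed event risks, on independence between periods and on the chosen test. An observed excess on VR is the expected tendency, not a certainty. The matter should be settled while data can still be collected in the same way under both treatments, but it affects a secondary aim only.

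**What to change.** **Preferred.** Ask the same adverse-event questions on the same weekly schedule in the 8-week glasses period, and add a brief item on glasses wear. The cost is about 8 short calls per amblyopic patient, or 8 x 30 = 240 in all, by the existing team, plus slightly more contact than usual care involves. The safety contrast should then rest on the questions common to both periods, with entries from the post-session gaming diary reported separately for VR.

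**Otherwise.** Base the VR-versus-glasses safety comparison only on events elicited with one identical checklist at the post-treatment visits, T2 and T4. Report VR diary and call events descriptively. Remove the standard-care comparison from the adherence part of aim d. This uses visits already planned and costs little, but it only reduces the bias: recall at the visit after VR will have been primed by the diary and calls, and the report should say so.

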### Data management

All collected data will be coded and subsequently entered and stored in REDCap [63, 64], a secure, web-based application designed to support data capture for research studies by building and managing online surveys and databases.

### Statistical analysis

Linear Mixed Models (Jamovi & R software) will be used to investigate primary and secondary outcomes before and after treatment, compared to refractive correction, and compared to the healthy control group. We will include BCVA and stereoacuity measured at baseline and age as covariates. If age shows a significant covariance effect, we will identify clusters of age-based differences and compare the groups directly by splitting the data and using age as a factor in the analysis. For the selective attention skills, multivariate analyses will also be performed to investigate changes in brain activity (CARTOOL [65], STEN software [66], FieldTrip toolbox [67], custom scripts in Python). To evaluate motor control skills, trajectory and velocity profiles using Statistical Parametric Mapping [68] will be determined. Structural Equation Modelling will be conducted to identify the individual and combined value of behavioral and electrophysiological changes in vision, selective attention, and motor control to predict improvements in vision functions (Onyx software).

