Aiming to increase compliance and treatment effectiveness, serious games delivered on tablets have recently been developed (serious games are games used for purposes other than mere entertainment [14]). More specifically, these games focused on binocular stimulation by using dichoptic images, where the contrast level of the image to the fellow eye is reduced to encourage binocular integration of complementary images, and as such to balance cortical input and overcome interocular suppression. Such dichoptic stimulation delivered on tablets seems to effectively improve visual acuity [15–19] and might be superior to occlusion therapy [15, 20]. Nevertheless, the additional recovery of stereovision (3D vision) seems to require further ingredients in the training. Three studies have shown an improvement in stereovision in adults with amblyopia when using one game in a Virtual Reality (VR) environment [21–24], suggesting that a VR-based training providing 3D cues and rich feedback may better target improvement in stereovision in both strabismic and anisometropic type of amblyopia, improving also treatment compliance [25]. However, these preliminary studies in adults delivered the VR in a lab environment and with only one or two games. A recent review showed that binocular perceptual learning and dichoptic videogames result in improved stereovision in adults with strabismus, compared to the null results seen with monocular versions of such stimulation [26]. This review gathers data from almost 100 adults with amblyopia and provides three conclusions: (1) more patients with anisometropic amblyopia improve compared to the strabismic type, (2) many more patients with strabismus have not measurable stereopsis before and after the training, compared to the anisometropic type, and (3) both types of amblyopia show improvements in stereopsis, regardless of their baseline stereoacuity, achieving stereoacuities of 140 arcsec or better. As such, we hypothesize that a VR-based training with the suggested ingredients (3D cues and rich feedback), combined with increasing the difficulty level and the use of various games in a home-based environment is crucial for treatment efficacy of vision recovery, and may be particularly effective in children.

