## Methods I: Participants, interventions, and outcomes

### Study design

This is a single-center, evaluator-masked, non-inferiority, cross-over Randomized Controlled Trial (RCT). This study is approved by the Ethical Cantonal Board of Geneva, Switzerland (CCER N° 2021-D0090) and all methods are performed in accordance with the relevant guidelines and regulations. The protocol for this study was designed according to the SPIRIT (Standard Protocol Elements: Recommendations for Interventional Trials) 2013 Statement [35, 36]. Recruitment of participants is planned from May 2022 to December 2024. The trial will take place in the Department of Ophthalmology of the Geneva University Hospitals (Switzerland). The amblyopic cohort will take part in the cross-over design. They will be randomly assigned to take part either first in the study-intervention arm and second in the control-treatment arm, or vice versa (AB or BA), stratified according to the type of amblyopia (anisometropic, strabismic or mixed). They are not masked to the order of the received training. The age-matched control cohort will only complete the VR-based intervention.

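### The stated covariates for the amblyopic crossover include neither a period term nor amblyopia type, the randomisation stratum; both should be written into the model or confirmed in the SAP

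*Protocol article*

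**What the plan says.** The Study design section sets a two-order crossover for the amblyopic cohort (AB is VR first, BA is glasses first), "stratified according to the type of amblyopia (anisometropic, strabismic or mixed"). The Allocation section repeats the stratification. On method it says that "The allocation sequence will be generated with computer-generated random numbers", and it gives no block size or ratio.

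The Statistical analysis section says "Linear Mixed Models (Jamovi & R software) will be used to investigate primary and secondary outcomes before and after treatment", with comparisons against refractive correction and against the healthy controls. It then adds: "We will include BCVA and stereoacuity measured at baseline and age as covariates". Age may later become a factor if it shows an effect. The section mentions neither period, nor sequence, nor amblyopia type.

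The Participant timeline gives five assessments, T1 to T5. T3 is both the follow-up of the first treatment and the pre-measure of the second. The Sample size section plans 24 evaluable patients and recruits 30 to allow for dropout.

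**The concern.** The article names an adjustment set, and that set does not mirror the design. In an AB/BA crossover, period is the standard nuisance term for the within-patient comparison. If baseline means T1, the three named covariates are constant within a patient and do little for that comparison. The factor used to stratify randomisation is also absent.

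A shift between periods is possible. T1 to T5 cover four 8-week intervals (4 x 8 = 32 weeks), participants may be as young as 6, and the same model serves reading, attention and reaching tasks that are repeated and open to practice. An unmodelled period difference widens the interval for the treatment contrast and, if the orders are unequal, shifts the estimate. Both matter in a trial that the article labels non-inferiority.

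**Working it through.** **The plan's own figure.** Inputs from the Sample size section: Cohen's f = 0.25, α = 0.05, power 80%. The number of measurements m and the within-patient correlation ρ are not stated. With the repeated-measures F test, λ = N·f²·m/(1 − ρ):

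- m = 4, ρ = 0.5: λ = 24 × 0.0625 × 4/0.5 = 12, power 0.817, and 24 is the smallest N that reaches 80%.
- m = 2, ρ = 0.65: power 0.801 at N = 24.
- Recruitment: 24 × 1.25 = 30.

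So 24 and 30 reproduce under assumed m and ρ. With m = 2 and ρ = 0.65, the standardised within-patient effect is 2f/√(2(1 − ρ)) = 0.5/√0.7 ≈ 0.6. That effect gives 80% power in a paired test at n = 24 and is used below.

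**Set-up.** Let d be a patient's VR-minus-control difference, with SD 1 within an order. Let τ be the treatment effect and δ the period effect (second period minus first), in units of that SD. The mean of d is τ − δ in AB and τ + δ in BA.

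**Precision if period is omitted (12/12).** The pooled variance of d is 1 + δ², so the estimated SE is multiplied by √(1 + δ²), and 24 patients are worth 24/(1 + δ²):

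| δ (assumed) | SE ratio | 24 patients are worth |
|---|---|---|
| 0.25 | √1.0625 = 1.03 | 22.6 |
| 0.50 | √1.25 = 1.12 | 19.2 |
| 0.75 | √1.5625 = 1.25 | 15.4 |

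Power for τ = 0.6 by simulation (20,000 runs per setting), without against with the period term:

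- δ = 0: 80% against 81%
- δ = 0.25: 79% against 80%
- δ = 0.5: 73% against 80%
- δ = 1: 50% against 80%

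Hand check at δ = 0.5: the estimated SE is √(1.25/24) = 0.228 and the critical value is 2.069 × 0.228 = 0.472. The estimate's true SD is √(1/24) = 0.204, and (0.6 − 0.472)/0.204 = 0.63, which corresponds to about 73%.

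**Bias if period is omitted.** The mean of d over all patients is τ + δ(n_BA − n_AB)/n. The sizes are:

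- 12/12: 0
- 10/14: 4/24 = 0.17δ
- 9/15: 6/24 = 0.25δ
- 13/17: 4/30 = 0.13δ
- 12/18: 6/30 = 0.20δ

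The splits are assumed. If allocation were unrestricted, the median imbalance would be 0.17 at n = 24 and 0.13 at n = 30; blocking within strata would make it smaller before dropout. In the simulation at 9/15 and δ = 0.5, the unadjusted estimate was off by about 0.125. With no true effect it rejected in 6.2% of runs, against 4.8% with the period term.

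**Amblyopia type.** A patient-level main effect enters both periods equally and cancels from d. In a simulated random-intercept model, the treatment estimate with and without type differed by less than 1e-14, and the mean SE was 0.211 in both.

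**The case against.** The strongest reply is that the article lists covariates, not a full model. It does not list treatment or the patient random effect either, and the described comparisons need both. The list is not called complete, the article is a condensed one, and crossover terms are commonly left to an SAP. This stands: a reader might infer that the analysis excludes period, but the text does not say so.

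A reader might also infer that leaving out type costs precision or biases the crossover contrast. It does neither in patients with both periods, as shown above. Type matters for patients with only one period and for between-patient comparisons.

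The Background remark that "more patients with anisometropic amblyopia improve compared to the strabismic type" should not be read as showing that type predicts visual acuity. It comes from a review of almost 100 adults, concerns stereovision and describes response to training. It bears on effect modification at most.

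Nor do the documents show that a period effect on BCVA is likely. Eligibility requires stable BCVA over 6 months, and untreated or newly diagnosed amblyopia is excluded. Each period has its own pre-measure, so if change is analysed, a level shift already present at T3 cancels and only a difference in the amount of change remains. This lowers the expected size for the primary outcome. It answers less for the repeated reading, attention and motor tasks.

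**Conclusion.** The point holds as an improvement to the stated model. The named adjustment set matches neither the crossover (no period) nor the stratified randomisation (no type). If period is in fact omitted, the loss is small for a small period effect (3% on the SE at δ = 0.25) and material for a moderate one (12% at δ = 0.5, with power falling from 80% to about 73% at n = 24). Bias needs a real period effect and unequal orders together. These sizes rest on assumed period effects, assumed splits and a standardised effect of 0.6; the documents give none of them. The planned 24 and 30 are unaffected. The case for type is consistency with the randomisation and proper handling of one-period patients, not a gain in the within-patient contrast.

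**What to change.** State the model for the amblyopic cohort: treatment, period, sequence and amblyopia type as fixed effects, age and baseline values as covariates, and patient as a random effect. If an SAP already says this, confirm it and refer to it. Sequence, like type, is constant within a patient and leaves the complete-data contrast untouched; it is listed so that the model mirrors the design. Label any treatment-by-type analysis exploratory, because its power at 24 to 30 patients over three types has not been examined.

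The cost is one sentence and a few degrees of freedom: one for period, one for sequence and two for the three-level type. In the simulation, including period when no period effect exists cost no noticeable power. All the variables are already collected.
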